To achieve these objectives, we will seek to answer the following questions:What adopted models of ESD exist and how do these relate to evidence-based recommendations?Can realised benefits of implementing ESD be quantified by defined measures of effectiveness: reduction in length of hospital stay, responsiveness of the service, amount of rehabilitation delivered, and changes in patient dependency?What site-, model-, and patient-level characteristics influence effectiveness of ESD services?What are the cost consequences of adopted ESD models?What contextual elements influence whether ESD is implemented in the first place and how do they shape the model of service adopted?What are the perceived outcomes of implementing ESD from the perspective of service users, clinicians, managers, and commissioners and how are these achieved in practice?What are the conditions that contribute to the successful implementation and sustainability of ESD in practice?

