#### Data collection and analysis

Work package 1 will involve analysis of historical prospectively collected SSNAP data from hospital and community providers across the East Midlands, West Midlands, East of England, and North of England strategic clinical networks. A key aim of WP1 is to investigate whether the degree to which an ESD service has adopted an evidence-based model is related to better patient care (measured by ESD responsiveness and rehabilitation delivered) and patient dependency (modified Rankin Scale) [26] as well as the influence of rurality of the ESD service location. Effects of ESD on length of hospital stay will also be investigated; however, this analysis will require a different calibration of the statistical model and will be dealt with separately. To conduct these analyses, we employ multilevel modelling as it is an appropriate technique when analysing outcome variables that are generated from a clustered/nested structure whereby the outcome under consideration is produced by patients in different ESD team/hospital settings.

The effectiveness of ESD will be measured with evidence-based metrics as defined by national clinical guidelines for stroke and that reflect outcome measures used in the original ESD trials [6, 7]. Measuring the effects that ESD teams have on their patients is a necessary first step to learning how ESD practices combine to generate differences between teams. Combining SSNAP clinical audit data at the patient level with post-acute organisational audit data at the ESD team level, we will attempt to measure the ‘true’ effects that ESD teams have on their patients by fitting two-level patients-within-teams multilevel models to patient and process outcomes where covariate adjustments are made for a range of patient and ESD team characteristics.

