#### Evaluating the effectiveness of ESD service provision

To investigate our study hypotheses, information about each ESD service collected by SSNAP in the 2015 post-acute organisational audit will be collated by the research team. This will include ESD team composition, capacity, workload, and organisational features, e.g. frequency of team meetings. ESD team models will then be analysed by comparing ESD service information with ESD consensus statements and national clinical guideline recommendations [2, 8, 17]. This will be the first step in the investigation of adoption of evidence-based core components, e.g. stroke specificity and multidisciplinary team composition. An ESD consensus score will be applied to each ESD team included in our multilevel modelling.

Additional variables in the model obtained from the 2016 SSNAP clinical data at the patient level will include age at admission, sex, pre-stroke independence, comorbidities, NIH Stroke Scale score on admission, type of stroke, and modified Rankin score at discharge from hospital [26, 27]. These reflect previously validated stroke case-mix models [28, 29]. Data variables at the ESD team level (in addition to the ESD consensus score) will include level of rurality and deprivation [30] as well as the grade/score of each discharging hospital as recorded by the SSNAP team (to account for the influence of the quality of inpatient care prior to ESD). A ‘team-size’ score will also be included (total whole time equivalent (WTE) units per member of staff). By including these ESD team-level ‘contextual variables’ in our analysis, we are assuming that they may not be homogeneous across the ESD teams and may impact upon service provision as well as patient outcomes. Moreover, multilevel modelling enables us to appreciate the variation in outcomes as a mixture of patient variability nested within ESD service provision variability. Effectiveness of ESD service provision will be measured with the following outcome variables: responsiveness (time from hospital discharge to first contact), rehabilitation intensity (total number of treatment days/total days with ESD), and stroke survivor outcome (modified Rankin Scale after ESD delivered).

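### The only rehabilitation outcome measures intensity, although the research question asks about amount, and the modified Rankin Scale is read at a time that can differ by team

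*Protocol article*

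**What the plan says.** Research question 2, at the end of the Background, lists the measures of effectiveness. After length of hospital stay they are "responsiveness of the service, amount of rehabilitation delivered, and changes in patient dependency". The key aim in Data collection and analysis asks whether adopting an evidence-based model "is related to better patient care (measured by ESD responsiveness and rehabilitation delivered", and then turns to dependency.

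Evaluating the effectiveness of ESD service provision defines three outcome variables for the team models. The first is "responsiveness (time from hospital discharge to first contact". The second and third are "rehabilitation intensity (total number of treatment days/total days with ESD), and stroke survivor outcome (modified Rankin Scale after ESD delivered".

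No outcome for total treatment is defined, and no fixed time after stroke or discharge is given for the modified Rankin reading.

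The same section lists the covariates. At patient level they are age, sex and "pre-stroke independence, comorbidities, NIH Stroke Scale score on admission, type of stroke, and modified Rankin score at discharge from hospital". For teams, "Data variables at the ESD team level (in addition to the ESD consensus score) will include level of rurality and deprivation", followed by the discharging hospital's grade and a team-size score. Neither list names days with ESD or time since stroke or discharge.

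**The concern.** The question and the aim are about how much rehabilitation patients receive. The outcome is how densely treatment is packed into the episode. A team that treats often over a short episode can score above a team that delivers more in total, so a result on the ratio alone does not answer research question 2. It also bears on the rurality hypotheses. The countervailing example under Table 1 predicts that rural patients get less therapy than urban ones, which reads most naturally as a statement about amount.

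For dependency, the end of ESD is the assessment point. A patient kept longer is assessed later in recovery. Adjusting for modified Rankin at hospital discharge aligns the starting level but not the time that has passed since.

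Both outcomes feed comparisons by consensus score and rurality, and the Cost-consequence analysis section takes modified Rankin changes by ESD model type as treatment effects. If duration goes with model type or rurality, part of an observed association could be duration.

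**Working it through.** The article states no ESD durations, sample size or effect size, so there is no figure to reproduce. All durations and recovery rates below are assumptions chosen to show the mechanism.

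**1. Intensity against amount.** Let T be treatment days, D days with ESD, and R = T/D.

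| Team A | Team B | Higher ratio | Higher amount |
|---|---|---|---|
| 10/14 = 0.714 | 20/42 = 0.476 | A | B (20 against 10) |
| 12/14 = 0.857 | 20/28 = 0.714 | A | B (20 against 12) |
| 10/14 = 0.714 | 30/42 = 0.714 | tie | B (30 against 10) |

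Since T = R × D, the orders are opposite exactly when R_A > R_B but R_A × D_A < R_B × D_B, that is, when 1 < R_A/R_B < D_B/D_A. In the first row R_A/R_B = 0.714/0.476 = 1.5 and D_B/D_A = 42/14 = 3, so the order reverses. With equal durations D_B/D_A = 1 and reversal is impossible. The third row shows that at constant treatment frequency the ratio does not move with duration at all.

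**2. Timing of the modified Rankin reading.** Time since hospital discharge = time to first contact + D. With first contact after 1 day, D = 14 gives day 15 and D = 42 gives day 43, which is 28 days apart.

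Suppose all patients follow one recovery curve after ESD starts, with gain = G × (1 − exp(−D/τ)):

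| G (points) | τ (days) | Gain at 14 days | Gain at 42 days | Difference |
|---|---|---|---|---|
| 0.5 | 60 | 0.10 | 0.25 | 0.15 |
| 0.5 | 30 | 0.19 | 0.38 | 0.19 |
| 1.0 | 60 | 0.21 | 0.50 | 0.30 |
| 1.0 | 30 | 0.37 | 0.75 | 0.38 |

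Under these assumptions timing alone gives 0.15 to 0.38 points.

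**3. When this reaches the consensus-score association.** A simulation used 30 teams of 60 patients and 2000 runs. Team mean duration was 28 days (SD 8), and the modified Rankin curve had G = 1.0 and τ = 30 with no team effect of the score. Treatment days were set to 8 + 0.3 × D. Team means were regressed on the score.

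| Correlation of duration with score | Score significant, modified Rankin | Score significant, ratio |
|---|---|---|
| 0 | 5% | 5% |
| 0.3 | 17% | 32% |
| 0.6 | 49% | 91% |

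Two cautions apply. This is a simple regression without the planned covariates, and treatment days carry no random variation, so the ratio column mainly shows how detectable the assumed correlation is. In those runs intensity really is lower in longer episodes. The point is that the ratio falls with the score while treatment days rise.

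**The case against.** The strongest reply is that intensity is a declared construct of the study. The Background describes ESD in terms of intensity, the formal programme theory in Conceptual framework refers to intensive rehabilitation at home, and Table 1 lists intensity as an intended outcome. A days-per-day ratio measures that properly. This stands, and the ratio should stay. What remains is that research question 2 asks about amount, and no outcome measures it.

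A reader might infer that stopping early raises a team's score. The documents do not support that as a general statement. It needs front-loaded treatment, or a fixed number of treatment days spread over a longer stay, and the article describes neither. At constant frequency the ratio is unchanged (10/14 = 30/42).

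A reader might also infer that teams will differ on these outcomes with no difference in effectiveness. That does not follow either. How long a team supports its patients may be part of the model under study, and modified Rankin at the end of the service is a coherent outcome of the whole service.

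It is also fair to say that any distortion needs duration to vary with consensus score or rurality, and the article reports no such link. In the simulation, zero correlation gives the nominal 5%. Finally, the team covariates are introduced as ones the model will include, so the list may not be exhaustive, and a full analysis plan may deal with timing. That limits the modified Rankin part to a sensitivity analysis. It does not touch the mismatch between the printed question and the printed outcome.

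**Conclusion.** The concern holds in a limited form. The mismatch between amount and intensity follows from the text and from arithmetic: the ratio cannot by itself answer the amount part of research question 2, and the two quantities can order teams oppositely when episode lengths differ.

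The modified Rankin part is a possibility. The definition lets assessment time differ by team, and discharge modified Rankin does not correct for that. The 0.15 to 0.38 points and the simulated percentages rest wholly on assumed durations, recovery curves and correlations. From the documents alone the size and direction of any effect on the consensus-score or rurality associations are unknown, and if teams keep patients for similar times it largely disappears. This is a gap worth closing because closing it is cheap. It is not evidence that the planned comparisons are invalid.

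**What to change.** 1. Keep treatment days divided by days with ESD as the intensity outcome.
2. Add total treatment days per patient as a separate amount outcome, in the same multilevel model with the same covariates. This is the numerator of the ratio, so no new data are needed.
3. Report days with ESD by team, so that readers can see whether episode lengths differ and whether they go with consensus score or rurality.
4. Interpret amount and intensity as distinct quantities. Do not require them to agree: at constant frequency amount rises in proportion to duration, so agreement would make intensity conclusions depend on episode length.
5. For modified Rankin, add one model, labelled as a sensitivity analysis, with team-median ESD duration as a team-level covariate. Use the team median because a patient's own duration is partly a result of recovery. If the consensus-score coefficient moves materially, report that timing and service model cannot be separated.

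The cost is one more outcome and one more model. The duration adjustment may remove part of a real team effect, so it does not replace the main model. The team median also leaves differences in hospital stay before ESD untouched.

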#### ESD impact on patient length of hospital stay

A key benefit of ESD identified in the original randomised controlled trials was a reduction in length of hospital stay [6, 7]. Hence, we have also included this measure in our proposed analysis. Using our multilevel modelling framework and controlling for our covariates, this analysis will examine how patient length of hospital stay is influenced by the presence or absence of an ESD service on their care pathway.

Independent of the ESD team data, 2015–2016 hospital SSNAP data will be analysed to determine if patients from admitting hospitals that have ESD available as part of their care pathway differ in total length of inpatient stay from patients from admitting hospitals that do not, whilst controlling for confounding variables (e.g. patient level characteristics highlighted above). For this analysis, patients will be nested within admitting hospitals rather than ESD teams, and hence, different datasets will be used. Hospital characteristics of interest are type of hospital (e.g. as recorded by the SSNAP team) and a measure of delayed transfers of care from hospital, derived from the Adult Social Care Outcomes Framework (ASCOF), to account for influence of provision of social care [30]. The outcome variable for these analyses will be hospital length of stay at the patient level.

An additional analysis using a difference-in-difference, i.e. before-and-after design, will then be conducted to further investigate the magnitude of ESD impact on patient length of hospital stay [31]. This will provide a comparative analysis to the previous cross-sectional approach whereby we compare that 2015–2016 time period with a previous time period (2013–2014) in terms of ESD prevalence and its impact on inpatient length of stay across the two time periods. Difference-in-difference analysis enables investigation of differences in length of hospital stay over time and comparison between sites that have implemented ESD with sites that have not. To do this, the analysis requires use of data collected before and after the implementation of ESD. In this study, implementation of ESD is measured in terms of ESD being offered as part of the patients’ care pathway, from their admitting hospital and across the two time periods. Furthermore, we will determine which admitting hospitals had ESD as part of their care pathway at each time period, using patient-level SSNAP data, which tracks patient journey from first inpatient admission to final discharge destination.

### Work package 2

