## Background

Stroke is one of the main causes of adult disability, and there is strong research evidence to show that provision of stroke specialist rehabilitation enhances recovery [1, 2]. Service delivery models that offer home-based stroke rehabilitation have gained increasing interest particularly as healthcare services face the challenge of cost reduction and integrated care provision [3–5].

Stroke Early Supported Discharge (ESD) is a multidisciplinary team intervention that facilitates discharge from hospital and delivery of stroke specialist rehabilitation at home and at an intensity equivalent to that provided in an acute stroke unit. Cumulative evidence from clinical trials has shown that ESD can reduce the length of hospital stay and the risk of dependency of stroke survivors [6, 7]. As a result, there is currently widespread implementation of stroke ESD services in the UK and other countries.

In England, National Clinical Guidelines from the Royal College of Physicians and the National Institute for Health and Care Excellence (NICE) recommend the provision of ESD as part of an evidence-based stroke care pathway [2, 8]. Yet, despite these research and policy drivers, national audit reports showed that the type of ESD services stroke patients receive is variable, and in some regions, ESD is still not offered at all [9]. Alternative models of operation have been adopted, but it is not known how close they are to the evidence-based models with demonstrated effectiveness in clinical trial settings. It remains unclear whether health and cost benefits of the ESD intervention are achieved when services are implemented in practice. With outcome-based commissioning becoming a priority within the National Health Service (NHS) in the UK, it is important to investigate whether ESD services are still effective in real-life clinical settings. Distinguishing between effective and ineffective implementation is crucial to address inequities in service provision and plan service improvements [10]. It is also vital with regard to informing implementation of sustainable evidence-based service models.

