To fulfil the study’s aim, the formal theory needs to be refined and preliminary realist hypotheses developed, codified into CMO conjectures, and tested through data collection. We drew on the work of Dalkin et al. [22] who suggested that explicitly disaggregating mechanisms into resources and responses highlights the difference between the intervention and generative mechanisms and facilitates the formulation of CMO configurations. We conceptualised the evidence-based core components of ESD services as the programme resources, and we will seek to surface the perspectives and behaviours of actors and stakeholders (staff and patients) who are making ESD happen on the ground. As intended outcomes, we used the process and patient outcomes examined by clinical trials and the national stroke audit, but we also allowed for exploration of unintended outcomes, mainly through the qualitative component of the study. Table 1 presents an initial CMO framework, which we will use to configure our realist hypotheses and examples of initial plausible scenarios. This example explores how the rurality of the location of the ESD service may lead to a facilitatory or countervailing interaction with mechanisms to generate intended or unintended outcomes. These hypotheses will be put to test through data collection and analysis in order to fine-tune underpinning CMO configurations and increase our understanding of how these elements are related [13]. This approach will be compared to existing implementation research frameworks, acknowledging the dynamic nature between an intervention’s core components, actors delivering the intervention, and the context in which this takes place [12, 20].

**Table 1 Tab1:** Programme theory CMO framework

Context	Mechanisms (resources + responses)		Outcomes
Rurality of ESD service location	Eligibility criteria		Accelerated transfer of care from hospital to home
	Team composition		
Commissioning and financial arrangements	Whole time equivalent staff/patient ratio	Staff perspectives/behaviour	Rehabilitation delivery—responsiveness
ESD provider organisation	Stroke specialism and staff training	Patient perspectives/behaviour	Rehabilitation delivery—intensity of rehabilitation
Referring services characteristics and locations	Multidisciplinary team co-ordination (e.g. meetings)		Patient outcomes—recovery

Example of a facilitatory CMO with intended consequences

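### The cross-sectional length-of-stay model takes its patient covariates from a list that includes modified Rankin score at hospital discharge, which leaves the estimated ESD effect open to bias

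*Protocol article*

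**What the plan says.** Under *Evaluating the effectiveness of ESD service provision*, the protocol article lists the patient-level covariates for the ESD-team models. Six are fixed at or before admission: age, sex, pre-stroke independence, comorbidities, admission NIHSS and stroke type. The seventh is the discharge score. The list closes with "NIH Stroke Scale score on admission, type of stroke, and modified Rankin score at discharge from hospital". The outcomes of those models are time from discharge to first contact, rehabilitation intensity, and modified Rankin score after ESD.

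Under *ESD impact on patient length of hospital stay*, the question is "how patient length of hospital stay is influenced by the presence or absence of an ESD service on their care pathway". Covariates are mentioned twice. The first mention is unrestricted: "Using our multilevel modelling framework and controlling for our covariates". The second points back to the list: "whilst controlling for confounding variables (e.g. patient level characteristics highlighted above"). On the outcome the section says: "The outcome variable for these analyses will be hospital length of stay at the patient level". It spells out three differences from the ESD-team models: nesting within admitting hospitals, other datasets, and hospital-level characteristics. It names no change to the patient-level covariates.

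**The concern.** A covariate can be a proper baseline in one model and a post-exposure variable in another. For the ESD-team outcomes, hospital discharge is the starting point, so modified Rankin score at discharge describes the patient at entry. For length of stay, discharge is the end point. The exposure, ESD on the admitting hospital's pathway, is in place before then, and the score is recorded as the stay ends.

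The *Background* section says: "Stroke Early Supported Discharge (ESD) is a multidisciplinary team intervention that facilitates discharge from hospital". If ESD changes when a patient leaves, it may also change how disabled that patient is on leaving. A variable that the exposure can change is not a confounder. Holding it fixed asks whether stays differ among patients who leave at the same level of disability. That is not the question posed, which concerns the total effect of having ESD on the pathway.

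The matter is not peripheral. The *Background* section names reduced hospital stay among the measures of effectiveness. Length of stay is also the only quantitative outcome compared with patients whose pathway has no ESD, since the ESD-team outcomes exist only for patients who reach an ESD team.

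**Working it through.** The article gives no sample size, effect size or coefficient for this analysis, so there is no figure to reproduce. The check is a reading of the cross-reference, followed by a formula showing what can and cannot be said about the bias.

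**Step 1. What the back-reference picks up.**

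| Patient-level item in the list | When fixed | ESD-team models | Length-of-stay model |
|---|---|---|---|
| Age, sex, pre-stroke independence, comorbidities, admission NIHSS, stroke type | At or before admission | Before the outcome | Before the outcome |
| Modified Rankin score at discharge | At discharge | Before the outcome | At the end of the outcome |

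Only the last row changes role between the models, and the article does not remove it.

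**Step 2. What adjustment does.** In a least-squares fit with the same admission covariates throughout,

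adjusted ESD coefficient = unadjusted ESD coefficient − α × β,

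where α is the ESD coefficient when discharge score is regressed on ESD and the admission covariates, and β is the coefficient of discharge score in the adjusted length-of-stay model. If ESD has no net association with discharge score (α = 0), nothing changes. Otherwise the shift has the sign of −αβ. The article gives neither α nor β.

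**Step 3. Why the direction is open.** The following inputs are all assumed. They show only that the sign can go either way and do not estimate the bias in this study.

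- *Linear model*: 200 hospitals of 300 patients, 20 repeats, true ESD effect −0.20 SD. Stay and discharge score both depend on admission severity and on an unmeasured recovery factor; the score is cut into six categories.
  - ESD raises the underlying discharge score by 0.2, and stay has no effect on it: −0.193 without the score, −0.252 with it. The shift is −0.252 − (−0.193) = −0.059, so the benefit is exaggerated.
  - ESD lowers it by 0.2, and each SD of stay raises it by 0.3: −0.205 without, −0.082 with. The shift is +0.123, so the benefit is attenuated.
- *Threshold model*: 200,000 patients, each discharged once disability falls to a personal threshold, which ESD raises.
  - Raised by 0.25 points: −2.28 days without the score, −0.81 with it (attenuated).
  - Not raised: 0.06 and 0.02 days (no material change).

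In the first linear case and in the first threshold case ESD raises disability at discharge, so α is positive in both. The shifts nevertheless have opposite signs, because β is positive in one (sicker patients stay longer) and negative in the other (patients kept longer leave less disabled). Knowing the sign of α alone would not settle the direction.

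**The case against.** The strongest reply is that the article never names discharge modified Rankin as a length-of-stay covariate. The pointer is introduced by 'e.g.' and limited to confounders, which this score is not. The unrestricted mention of covariates cannot mean the whole set either: the ESD consensus and team-size scores do not exist for hospitals without ESD, and the analysis is said to be independent of the ESD-team data, so some selection is implied. *Data collection and analysis* adds that the length-of-stay model will be calibrated differently and handled separately. A condensed article may leave the final list to an analysis plan.

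Part of this stands. The wording leaves discretion, so a reader who infers that the score will certainly be entered, and that the estimate is therefore biased, goes further than the text. But the implied selection concerns team-level variables. For patient-level variables the article does give a rule, and followed as written that rule includes the score. This is a stated set with one unsuitable member, not a detail left out.

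Three further inferences are tempting, and the article does not support them.

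- *That the difference-in-difference analysis has the same fault.* Its description names no covariates.
- *That the delayed-transfer covariate is also on the causal path.* The model includes "a measure of delayed transfers of care from hospital, derived from the Adult Social Care Outcomes Framework (ASCOF"), and Table 1 lists "Accelerated transfer of care from hospital to home" as an intended outcome. Nothing equates the two. The measure carries a stated reason, the influence of social care provision, and has no stated date.
- *That the benefit is understated by some number of days.* Any such figure comes from assumed inputs.

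**Conclusion.** The point holds in limited form. Read as written, the cross-sectional length-of-stay model may adjust for a variable recorded after exposure and at the end of the outcome, and nothing in the article excludes it. The estimated total effect of ESD availability is then open to bias.

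This rests on two things: that the back-reference is followed literally, and that ESD availability changes disability at discharge. The second is inferred from the description of ESD as facilitating discharge; the article does not state it. Size and direction cannot be determined from the document, and if ESD availability has no net association with discharge score, given the admission covariates, the adjustment does no harm. The point is worth correcting before analysis because the correction is easy and the outcome is a named measure of effectiveness. It does not show that any result is wrong.

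**What to change.** Replace the back-reference with an explicit list. State that the length-of-stay model adjusts at patient level only for variables fixed at or before admission: age, sex, pre-stroke independence, comorbidities, admission NIHSS and stroke type. State that modified Rankin score at discharge is used in the ESD-team models only. If covariates enter the difference-in-difference analysis, apply the same restriction there. The hospital-level covariates can stay as planned.

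The cost is one sentence and slightly less variance explained in the length-of-stay model. All six variables are already on the article's list, so the change adds no new covariate.
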